## Abstract

**Background::**

Cardiovascular disease (CVD) poses a substantial global health burden, necessitating effective and scalable interventions for primary prevention. Despite the increasing recognition of peer-based interventions in managing chronic diseases, their application in CVD prevention still needs to be explored.

**Aims::**

We describe the protocol of a quasi-experiment to evaluate the effectiveness of a peer-led digital health lifestyle intervention, MYCardio-PEER, for a low-income community at risk for CVD. This study aims to assess the effectiveness of MYCardio-PEER in improving the participants’ knowledge, lifestyle behaviours and biomarkers related to CVD. Secondarily, we aim to assess the adherence and satisfaction of participants towards MYCardio-PEER.

**Methods::**

A minimum total sample of 68 low-income community members at risk for CVD will be recruited and allocated either to the control group or the intervention group. Participants in the control group will receive standard lifestyle advice and printed materials for CVD prevention, while the intervention group will participate in the 8-week MYCardio-PEER intervention program. The participants will be assessed at Week 0 (baseline), Week 8 (post-intervention) and Week 20 (post-follow-up).

**Discussion::**

We anticipate a net improvement in CVD risk score, besides investigating the effectiveness of the intervention program on CVD-related knowledge, biomarkers, and diet and lifestyle behaviours. The successful outcome of this study is essential for various healthcare professionals and stakeholders to implement population-based, cost-effective, and accessible interventions in reducing CVD prevalence in the country.

**Trial registration**: ClinicalTrials.gov (NCT06408493)

## Introduction

Cardiovascular disease (CVD) has been identified as the primary cause of mortality worldwide (Vaduganathan et al., 2022), exhibiting a higher prevalence in low-income countries (LICs) with 7.1 cases per 1000 person-years, and middle-income countries (MICs) with 6.8 cases per 1000 person-years compared to High-Income Countries (HICs) with 4.3 cases per 1000 person-years (Dagenais et al., 2020; Vaduganathan et al., 2022). In Malaysia, CVD also stands as the major contributor to the premature mortality rate, with ischaemic heart disease as the principal cause of death, which recorded 20 322 deaths (16.1%) in 2022 (DOSM, 2020a). To address this pressing issue, the Malaysian government has been actively promoting a healthy lifestyle using advertisements and awareness programs to educate the public and patients about the significance of being aware of their CVD risks (MOH, 2017). Despite these efforts, the prevalence of CVD risk factors, including hypertension, dyslipidaemia, and diabetes, continues to rise among Malaysians, as reported in the recent Malaysian Health and Morbidity Survey (NIH, 2019).

Lifestyle risk factors such as unhealthy diet, physical inactivity, tobacco use, and alcohol consumption significantly contribute to the escalating prevalence of CVD (CDC, 2021). Consequently, lifestyle modifications remain pivotal in the primary prevention of CVD, especially among high-risk populations (Rippe & Angelopoulos, 2019; Kaminsky et al., 2022). While lifestyle interventions targeting these adverse health behaviours have shown promise, their implementation in community settings faces challenges such as workforce limitations, cost considerations, program acceptability, and cultural adaptation (Milat et al., 2014). Furthermore, healthcare professionals may lack the necessary skills, time, and socio-cultural understanding to provide ongoing support and empowerment for behavioural change in managing CVD risk factors (Moudatsou et al., 2020). Therefore, the role of social environment and support in facilitating practical behaviour change interventions within the community is crucial (Latkin & Knowlton, 2015).

Peer support, where individuals with similar backgrounds and experiences provide support, is vital in promoting and maintaining complex health behaviours and managing non-communicable diseases (NCDs) (Fisher et al., 2017; Fortuna et al., 2019). Peers offer a sense of community and ongoing emotional support, enhancing motivation to overcome barriers to behaviour change (Fisher et al., 2023). Recent advances in peer support have expanded its functions to include assistance in daily disease management and acting as a link to clinical and community resources (Evans et al., 2021). A recent systematic review evaluated and reported favourable effects of peer-led interventions on the primary prevention of CVD (Lim et al., 2024). However, peer-led intervention as a viable community approach to prevent CVD still needs to be explored among the low-income communities in Malaysia.

Digital technologies, particularly those using bite-sized videos and infographics, offer a promising solution for ensuring the scalability and accessibility of peer-led interventions. Digital technologies have emerged as powerful tools in healthcare, offering innovative ways to deliver interventions and engage individuals in managing their health (Stoumpos et al., 2023). The widespread use of smartphones and internet access has created unprecedented opportunities to reach populations traditionally underserved by organised healthcare services (Xiong et al., 2023). Videos, for example, can deliver information in a visually engaging and interactive format, making complex concepts easier to understand and remember (Tuong et al., 2014). By incorporating evidence-based guidelines, these videos can educate individuals about modifiable risk factors for CVD and provide practical strategies and step-by-step guidance on adopting healthier habits, thus empowering individuals to take control of their cardiovascular health.

Despite the benefits of peer support and digital technologies, no interventional study in Malaysia integrates both, and none of the CVD primary prevention interventions have focused on low-income communities (Raman et al., 2024). There is a clear research gap regarding the application of peer-led digital health lifestyle interventions for managing CVD risk, particularly among the low-income community in Malaysia. Hence, we have designed a quasi-experimental study to evaluate the effectiveness of a peer-led digital health lifestyle intervention, MYCardio-PEER, for a low-income community at risk for CVD. This study aims to assess the effectiveness of MYCardio-PEER in improving the participants’ knowledge, lifestyle behaviours and biomarkers related to CVD, and to assess the adherence and satisfaction of participants towards MYCardio-PEER.

## Materials & methods

### Study design

This study will adopt a quasi-experimental study design. As this intervention study relies on peer support, a quasi-experiment is considered the most appropriate study design due to the practical barrier for randomisation, including participants’ locality and peer connectivity (White & Sabarwal, 2014). The study protocol was developed in accordance with the Transparent Reporting of Evaluations with Nonrandomized Designs (TREND) statement and checklist as presented in Supplementary Table 1 (Des Jarlais et al., 2004). This study has been registered on ClinicalTrials.gov (NCT06408493).

### Study flow

This study is to be completed in 20 weeks, comprising an initial eight-week core intervention aimed at promoting health behaviour adoption (Bajer et al., 2019), followed by a 12-week follow-up period post-intervention to evaluate its sustainability (Khouja et al., 2020). Figure 1 depicts the flow chart of the proposed study. Local community members will be invited to medical camps that will be used as screening and recruitment camps for the quasi-experiment study. Upon completion of the baseline assessment at Week 0 (T0), the participants will be assigned into two groups: intervention or control. The intervention will be conducted for eight weeks, followed by the post-intervention assessment at Week 8 (T1). The post-follow-up assessment will be conducted at Week 20 (T2), whereby there will be no active intervention within the 12 weeks.

**Figure 1. f1:**
[figure not shown]
Flow chart of the proposed study.

The intervention lasts for eight weeks, allowing time for participants to acquire CVD-related knowledge and self-regulation skills with peer support, thus improving the proximal outcome in terms of CVD risk factors and lifestyle behaviours. As for the 12 weeks of no intervention period, it is necessary to evaluate whether participants maintain the adopted behaviours autonomously and whether the initial intervention effects persist over time in improving the distal outcome of cardiovascular health (Ryan, 2009; Gold et al., 2021). The participants’ adherence and satisfaction with the intervention program will also be assessed at T2. Peer leader coaching based on the Peer for Progress training module (Peer for Progress, 2021) will be provided to the selected community leaders before the intervention.

### Setting

Our study will be conducted in Kulim, Kedah, Malaysia, in collaboration with the Kamakshi Welfare and Social Association (KWSA). Kedah, a state in the country’s northern region, is not only identified as one of the economically challenged states (DOSM, 2020b). Its population also has the highest CVD risk score based on region-specific analysis (Che Nawi et al., 2022). Furthermore, Kulim is among the administrative districts in Kedah that exhibit a high poverty rate, which has been on the rise from 2019 to 2022 (DOSM, 2023).

In conjunction, KWSA located in Kulim, Kedah, actively engages in community outreach initiatives that primarily assist single, marginal, or economically disadvantaged individuals by providing career guidance, financial assistance, nutritious foods and essential household items (PKDS, n.d.). Within this context, KWSA has good acquaintances with the community’s needs. By partnering with KWSA, this study can leverage their deep understanding of the local low-income community and their established presence in the area, thus ensuring that the intervention is tailored to the unique circumstances and preferences of the target population, maximising its potential impact and effectiveness. In return, the findings from the current study can contribute to the implementation of personalised health interventions within this community.

### Participants

#### Sampling and recruitment

Convenience sampling complemented by snowball sampling techniques will be employed for this study. Firstly, we collaborated with KWSA as the grassroot organisation to disseminate the information about the medical screening camp to the community members in their contact database list. The medical screening camp is part of a larger study to identify individuals at moderate to high risk of CVD. Secondarily, participants in the screening camp will be encouraged to extend invitations to other potential participants through personal recommendations. This combined approach ensures our study reaches the target population by utilising established community networks and connections, making the research culturally appropriate and community-focused (Valerio et al., 2016). It also facilitates the formation of peer groups for the intervention, fostering trust and rapport, increasing engagement in peer-led activities that promote lifestyle behavioural change.

During the medical screening camp, we will obtain socio-demographic information, anthropometry measurements, clinical measures, and calculated Framingham General CVD Risk Score (FRS). By matching the eligibility criteria, explanatory statements and consent forms about the study will be provided to recruit the potential participants. Informed consent to participate in the study will be obtained before baseline data collection. The minimum age of 30 years was set to align with the applicability of the FRS, which is designed for individuals aged 30 years and older. Table 1 shows the eligibility criteria of study participants.

**Table 1. tbl1:** Eligibility criteria of study participants

Inclusion	Exclusion
Mentally sound individuals of at least 30 years old	Pregnant, lactating or intend to become pregnant during the study period
Have a monthly household income of less than RM3,710 [30] or receiving government aid for low-income community	Have other pre-existing medical conditions or severe complications which could compromise the ability to adhere to the study
Literate with a fair command of the Malay language	Have been enrolled in other studies
Have a mobile device connected to the Internet	
Willing to attend eight weeks of intervention and be followed up for another 12 weeks during the maintenance phase	
Have been confirmed to have a moderate or high risk for CVD based on the Framingham General CVD Risk Score (FRS) [4]	

Peer leaders will be selected from within the same community and screened for moderate to high risk of CVD. This ensures that the leaders share relevant experiences with the target population. The selection process will include discussions and recommendations by the social welfare centre to assess candidates’ leadership and communication skills. Additionally, personal interviews will be conducted to further evaluate their suitability and commitment to supporting the program’s objectives. Candidates will also undergo training to equip them with the necessary skills to facilitate intervention activities and encourage behaviour change.

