### Participant allocation

Two groups will be under study for this quasi-experiment: the intervention group and the control group. The recruited participants will be allocated into one of the two groups based on their geographical location to ensure participants’ convenience when participating in the intervention activities. The participants in the intervention will be further divided into five subgroups, each consisting of six to seven members based on their peer connectivity. The non-random allocation considers familiarity and peer support, which are expected to lead to higher engagement levels in the intervention activities, promoting better adherence to the intervention and potentially more significant lifestyle behavioural changes.

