#### Control group

Participants in the control group will receive personalised lifestyle advice from a registered nutritionist at baseline, and standard printed materials on CVD prevention and healthy lifestyle habits. The control group participants will only be contacted for re-assessment at T1 and T2. The intervention content of MYCardio-PEER and peer support will not be provided to the control group.

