**Figure 2. f2:**
[figure not shown]
Conceptual framework of the intervention program.

The peer leaders will distribute evidence-based bite-sized educational videos and infographic posters developed for MYCardio-PEER via a WhatsApp group chat platform each week. These multimedia materials will comprehensively address topics related to knowledge dissemination, nutritional guidance, and lifestyle modifications pertinent to CVD prevention. The general topics and objectives of digital content are presented in Table 2. Within the week, peer leaders will also introduce interactive activities through the group chat or organise face-to-face sessions to enhance learning and practice behaviours. In the group chat, participants will be encouraged to pose questions, challenges, or experience sharing relevant to reducing CVD risk.

**Table 2. tbl2:** Topics and objectives of MYCardio-PEER intervention by week

Week	Topic	Objectives
1	Are you at risk of heart disease?	Identify the modifiable risk factors associated with CVD
2	Say YES to physical activity	Encourage the adoption of an active lifestyle
3	How to maintain a healthy weight?	Achieve and maintain a healthy body weight
4	Control your blood pressure	Obtain practical diet and lifestyle strategies for controlling blood pressure
5	Keep your cholesterol in check	Obtain practical diet and lifestyle strategies for maintaining healthy cholesterol levels
6	The not-so-sweet truths	Obtain practical diet and lifestyle strategies for maintaining healthy blood glucose levels
7	Enjoy living smoke-&-stress-free	Encourage a smoke-free lifestyle Enhance stress management
8	Practical tips for heart-healthy meals	Encourage the adoption of healthy eating habits that align with dietary guidelines for cardiovascular health

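### Invitations follow personal ties but the arm follows locality, so linked people can fall into opposite arms, and no described data would show whether controls saw the programme's material

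*Protocol article*

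**What the plan says.** All references are to the protocol article.

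- **Sampling and recruitment.** Recruitment starts from the partner association's contact list and is extended by snowballing: "participants in the screening camp will be encouraged to extend invitations to other potential participants through personal recommendations". No locality limit on the invitee is stated. One stated benefit of the combined approach is that "It also facilitates the formation of peer groups for the intervention".
- **Study flow.** Allocation comes after the camp, consent and baseline: "Upon completion of the baseline assessment at Week 0 (T0), the participants will be assigned into two groups: intervention or control".
- **Participant allocation.** "The recruited participants will be allocated into one of the two groups based on their geographical location". The reason given is "to ensure participants’ convenience when participating in the intervention activities". Separation of the arms is not mentioned as a purpose.
- **Setting.** The whole study takes place in one district with one partner association.
- **Intervention program.** "The peer leaders will distribute evidence-based bite-sized educational videos and infographic posters developed for MYCardio-PEER via a WhatsApp group chat platform each week".
- **Control group.** "The intervention content of MYCardio-PEER and peer support will not be provided to the control group".
- **Table 1.** Every participant, including every control, must have an internet-connected mobile device.
- **Outcome measures, Data collection and Process evaluation.** The process evaluation is for intervention participants only.
- **Discussion, limitations.** Selection bias from geographical allocation, self-report and residual confounding are listed. Contamination is not.

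**The concern.** Two rules use different criteria. Who enters the study depends partly on personal ties; which arm a person joins depends on where they live. If an inviter and an invitee live in different allocation areas, the two rules together can put two people who know each other into opposite arms.

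The digital part of the programme is short videos and posters in a group chat, which are easy to forward. The statement about the control group governs what the study provides. It does not address what participants pass on themselves.

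If controls receive effective content, the control arm moves towards the intervention arm. The difference in Framingham risk score change, and the differences in knowledge and behaviour, would then be understated. With the data described, a null result could not be separated into an ineffective programme and a diluted contrast.

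**Working it through.** **Step 1: can linked people end up in opposite arms?**

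| Element | What the article fixes | Consequence |
|---|---|---|
| Who invites | Camp attendees, before allocation | No inviter has an arm yet |
| Who may be invited | Personal contacts, no locality limit | An invitee may live elsewhere |
| What sets the arm | Geographical location, after baseline | Different areas can mean different arms |
| Catchment | One district, one association | Ties across areas are plausible |
| Delivery | Weekly WhatsApp videos and posters | Can be forwarded |
| Check on controls | None described | Exposure would not be seen |

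A cross-arm link arises only if the inviter enrols and lives in one arm's area, and the invitee enrols and lives in the other's. The article permits this chain but gives nothing from which to estimate how often it would occur.

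**Step 2: the plan's own sample size.** The inputs, from the sample size section, are an effect size of 0.25, 80% power, two-sided 0.05, 28 per group, and 34 per group after 20% attrition.

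- The 34 follows from 28 × 1.2 = 33.6, rounded up. Dividing by the retained share gives 28 / (1 − 0.2) = 35.
- The 28 cannot be confirmed, because neither the test family nor the correlation between repeated measures is stated. Reading 0.25 as Cohen's f, a group-by-time interaction test with three time points needs 54 in total at correlation 0 (27 per group), but 28 in total at correlation 0.5.

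The point does not depend on these figures. They matter only for turning dilution into power.

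**Step 3: size of the dilution.** Let c be the share of controls exposed and k the share of the full effect that an exposed control receives. Both are assumptions; the document gives neither.

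Remaining contrast = 1 − c × k.

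With k = 1, the upper bound for each c, the contrast is 1 − c and the required sample size rises by 1 / (1 − c)². Taking 28 per group as giving exactly 80% power, power under a normal approximation is Φ[(1.960 + 0.842)(1 − c) − 1.960].

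| c (assumed, k = 1) | Contrast left | Sample size factor | Power at 28 per group | Evaluable per group for 80% | Recruited per group, n / 0.8 |
|---|---|---|---|---|---|
| 10% | 90% | 1.23 | 71% | 35 | 44 |
| 20% | 80% | 1.56 | 61% | 44 | 55 |
| 30% | 70% | 2.04 | 50% | 58 | 73 |

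Partial transfer does less harm. For c = 20% and k = 0.5, the contrast left is 1 − 0.2 × 0.5 = 90%, the same as 10% full exposure.

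**Step 4: sensitivity to the unknown power basis.** If the analysis were the interaction test at correlation 0.5 with 56 evaluable participants, power would be 98.7% without dilution and 96%, 91% and 82% at c = 10%, 20% and 30%. The loss of power therefore depends on an unstated basis. The proportional bias in the estimate does not.

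**The case against.** **Sequence.** A reader might infer that intervention participants recruit their own contacts into the control arm. The document does not support this. Invitations come from camp attendees before anyone has an arm. The camp also belongs to a larger study, so some inviters may never enrol in this one. This objection stands, and the point is limited to people later allocated to opposite arms.

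**The design pulls the other way.** Allocation by area tends to keep neighbours together, and recruitment through existing connections is meant to help form peer groups. Linked people will often land in the same arm. This also stands: the risk is reduced, but not removed.

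**No contradiction.** It is tempting to say that the recruitment rule breaks the statement that controls are not given the content. It does not. That statement concerns what the study provides; forwarding between participants is a residual risk.

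**Silence in a condensed article.** Referral logs, area boundaries and forwarding instructions may be in a fuller document. It would therefore be wrong to say that contamination can never be examined. What can be said is narrower: the recruitment and allocation rules are stated here, the process evaluation is stated to cover intervention participants only, and the limitations omit contamination.

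**Full transfer is unlikely.** The programme also has peer leaders, group activities, an exercise club and food demonstrations, which a forwarded clip does not deliver. Nothing shows that seeing such a clip would move a risk score by the full effect. This stands, so the factors 1.23, 1.56 and 2.04 are upper bounds for their c and not forecasts.

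**Other routes.** Ties within the association's contact list exist without snowballing. A referral rule alone would leave them, which is why exposure should also be measured.

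**Conclusion.** The point holds as a risk that the described design leaves open. It is not a demonstrated bias. The recruitment and allocation rules allow linked people to fall into opposite arms, the material can be passed on, and the data collection described would not show it. The direction is towards no effect, provided that the programme works and that exposed controls respond in the same direction.

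The size cannot be derived from the document. Under the upper-bound assumption of full transfer, a share c of exposed controls leaves 1 − c of the contrast. The accompanying fall in power to 71%, 61% or 50% also assumes that 28 per group gives exactly 80%, which cannot be confirmed. This is a low-cost improvement worth making before recruitment.

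**What to change.** 1. In the section on sampling and recruitment, ask attendees to invite people from their own locality. Record each recruit's referrer and locality at the camp.
2. Ask intervention participants not to forward programme material during the study.
3. Add a control-exposure item at T2, or at T1 and T2 if it is worded neutrally, for example by asking which sources of heart-health information were received. A T1 item naming the programme would tell controls that it exists before the T2 assessment.
4. Report the share of controls exposed and the number of cross-arm referral links. Keep the comparison as allocated as the main analysis. Do not rely on excluding exposed controls: exposure arises after allocation and is probably related to how connected or health-interested a person is, so exclusion would add selection to a comparison that is already non-random.
5. Name contamination among the limitations.

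The cost is a slightly smaller referral pool, a referrer-and-locality entry on the camp form and one questionnaire item. The reduction in the pool cannot be quantified from the document.
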